#### Secondary outcomes (follow-up) – activity and participation

Fall rates may increase with increasing physical activity and mobility [54–60]. It is likely that when an individual with reduced balance control attempts to mobilize, s/he is at increased risk of losing balance and falling [61, 62]. Therefore, it is important to determine if fall rates are influenced by physical activity [63]. Conversely, improved balance control and reduced fear of falling should increase participation in activities. Physical activity and participation will be evaluated with the Physical Activity Scale for Individuals with Physical Disabilities (PASIPD [64]) and the Subjective Index of Physical and Social Outcome (SIPSO [65]), respectively, at six time points (every two months) during the 12-month follow-up. Regular administration of the questionnaires will provide an estimate of physical activity and participation over the duration of the follow-up period. The PASIPD is a 13-item questionnaire in which participants are asked to indicate the frequency and duration of recreational, household, and occupational physical activities completed in the previous 7 days. The PASID has been validated within a group of individuals with various physical disabilities, including those with stroke, showing good test-retest reliability (ρ = 0.77) and criterion validity when compared to accelerometer-based activity monitoring (ρ = 0.30; [66]). The SIPSO is a 10-item questionnaire that evaluates physical and social integration and participation in ‘normal’ daily life [65]. The SIPSO has good internal consistency (Cronbach’s α = 0.92) and test-retest reliability (ICC = 0.91) among those with stroke [65].

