
### Statistical analysis and sample size

Negative binomial regression will be used to compare fall rates between the two groups and logistic regression will be used to compare the proportion of fallers between the two groups. If the groups differ on prognostic factors (e.g., stroke severity) or on physical activity during the follow-up period (i.e., PASIPD scores) then multiple negative binomial/logistic regression will be used. Intent-to-treat analysis will be used; all individuals with some falls-monitoring data will be included in the analysis. Survival analysis may be considered if a large number of individuals do not complete the entire 12-month follow-up. Exploratory per-protocol analysis and/or comparison of fall rates between those who return for the ‘booster’ training sessions and those who do not may also be conducted. Repeated-measures analysis of variance, with group-by-time interaction, will be used to evaluate the effect of the interventions on secondary outcome measures (e.g., functional balance measures, balance confidence). The interaction effect will reveal if there is a greater pre- to post-training improvement in the perturbation training group compared to the control group.

The target sample size has been estimated using a formula for negative binomial regression described elsewhere [78]. Assuming a rate of falls in the control group of 1.75 per person per year [27], a reduction in rate of falling of 46 % in the perturbation training group [35], mean follow-up time of 11 months per person (i.e., some participants will be lost to follow-up before 12 months), level of significance (α) of 0.05, and power (1-β) of 0.8, we estimate that 37 participants per group will be required to show significant effects. From previous studies [32, 79], we expect that ~20 % of individuals will withdraw prior to completing the intervention. While many of these individuals will be willing to complete the 12-month falls monitoring period and could be included in intent-to-treat analysis, we conservatively assume that 20 % of individuals will withdraw from the study. Therefore, we will aim to recruit at least 46 participants per group (i.e., 92 participants total).

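### An activity questionnaire that correlates only 0.30 with measured activity decides whether the primary fall models are adjusted

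*Protocol article*

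**What the plan says.** In the Protocol article, the section on activity and participation explains that falls may rise with activity, and that better balance should in turn raise participation. It concludes: "Therefore, it is important to determine if fall rates are influenced by physical activity". The instrument chosen for activity is the PASIPD, a 7-day recall questionnaire given "at six time points (every two months) during the 12-month follow-up". Its properties are described as "showing good test-retest reliability (ρ = 0.77) and criterion validity", the second of these given in full as "criterion validity when compared to accelerometer-based activity monitoring (ρ = 0.30"). Table 2 lists no other measure of the amount of physical activity during follow-up; the SIPSO covers participation.

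The section on statistical analysis and sample size names negative binomial regression for fall rates and logistic regression for the proportion of fallers. It then makes the form of both models conditional: if the groups differ on prognostic factors "or on physical activity during the follow-up period (i.e., PASIPD scores) then multiple negative binomial/logistic regression will be used". It gives no test, threshold or significance level for deciding that they differ.

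**The concern.** Two uses of the PASIPD depend on how well it tracks activity. It is the switch that decides whether the fall models change, and it is the covariate in the changed model. An instrument that shares 9% of its variance with measured activity is weak for both. As a switch, it will often stay off when the groups do differ in activity, and will sometimes come on by chance. As a covariate, it leaves most of an activity difference in place.

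At stake is the form of the primary-outcome model, which would depend on a noisy comparison made during follow-up. Also at stake is what may be said about activity: a quiet PASIPD comparison cannot show that the groups were equally active, and a PASIPD-adjusted rate ratio cannot be presented as adjusted for activity.

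**Working it through.** **Inputs from the Protocol article.** Criterion correlation 0.30; test-retest reliability 0.77; six administrations; α = 0.05; 37 per group needed and 46 per group recruited.

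**The plan's own figures.** It gives no power for the PASIPD check and no estimate of what adjustment removes. Its group sizes do reproduce. The inputs are "Assuming a rate of falls in the control group of 1.75 per person per year", "a reduction in rate of falling of 46 % in the perturbation training group" and "mean follow-up time of 11 months per person", so the rates are 1.75 and 1.75 × 0.54 = 0.945. Then n = (1.960 + 0.842)² × (12/11)(1/1.75 + 1/0.945) / (ln 0.54)² = 36.75, or 37. This holds with the dispersion set to zero, which is a separate matter. Withdrawal: 37/0.8 = 46.25, stated as 46.

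**Assumptions for the rest.** Groups differ means p < 0.05 in a two-sided t-test. PASIPD error is classical and unrelated to group. The accelerometer represents true activity.

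**Step 1: does repetition help?**
- Shared variance of one score: 0.30² = 0.09.
- Reliability of the six-score mean (Spearman-Brown): 6 × 0.77 / (1 + 5 × 0.77) = 0.953.
- Its correlation with activity: 0.30 × √(0.953/0.77) = 0.334; squared, 0.111.
- Limit with unlimited repeats: 0.30/√0.77 = 0.342.

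**Step 2: chance that a true difference is flagged.** A true difference of d SD appears as ρ × d SD on the PASIPD. Power by the noncentral t distribution:

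| True difference | n per group | Perfect measure | Six-score mean | One score |
|---|---|---|---|---|
| 0.5 SD | 46 | 66% | 12% | 11% |
| 0.5 SD | 37 | 56% | 11% | 10% |
| 0.8 SD | 46 | 97% | 24% | 21% |

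The perfect-measure column separates the instrument from the sample size: even a perfect measure misses a 0.5 SD difference 34% of the time with 46 per group and 44% with 37.

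**Step 3: share of the activity-related effect removed.** If adjustment is always made, the expected share is ρ², which is 9% for one score and 11% for the six-score mean. The plan adjusts only when a difference is seen, so the triggered share must be found conditionally. Simulation (46 per group, linear outcome, six-score mean, 40,000 trials per setting):

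| True difference | Trigger fires | Removed if always adjusted | Removed when triggered | Average under the rule |
|---|---|---|---|---|
| 0.5 SD | 12% | 11% | 32% | 4% |
| 0.8 SD | 24% | 11% | 22% | 5% |
| 1.0 SD | 35% | 11% | 18–19% | 6% |

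The triggered share is higher because the trigger selects trials in which chance has enlarged the observed difference. The last column is roughly the product of the trigger and triggered columns, for example 0.12 × 0.32 ≈ 0.04.

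**Step 4: illustration.** Suppose a direct rate ratio of 0.54, activity 0.5 SD higher in the trained group, and 0.6 log units of fall rate per SD of activity (the last two assumed). The activity part is 0.5 × 0.6 = 0.30 log units and the crude ratio is 0.54 × e^0.30 = 0.73. Carrying over the linear shares, unconditional adjustment gives 0.54 × e^(0.30 × 0.89) = 0.71, and triggered adjustment about 0.54 × e^(0.30 × 0.68) = 0.66. Full adjustment would give 0.54.

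**Step 5: if the accelerometer is imperfect.** Suppose it correlates 0.6 with true activity (assumed). The validity becomes 0.30/0.6 = 0.50 for one score and 0.334/0.6 = 0.56 for six. Unconditional removal rises to 25–31%. Power with 46 per group becomes 22–26% at 0.5 SD and about 48–57% at 0.8 SD.

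**The case against.** The strongest reply is that the default analysis is the unadjusted randomised comparison, which the validity of the PASIPD cannot bias. On the article's own reasoning, activity may be a consequence of better balance. The crude 0.73 in the illustration would then be the total effect of training, and failing to move it to 0.54 would be no error. This stands. A reader might infer that the weak questionnaire distorts the primary result; the documents do not support that.

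A reader might also infer that adjustment, when used, removes only about a tenth. That is the figure for adjustment made regardless; under the stated condition it is about a fifth to a third, still a minority.

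The article nowhere says that a non-significant PASIPD comparison will be read as equal activity, or that an adjusted ratio will be called activity-adjusted. Those are risks of interpretation, not stated intentions. Nor does a weak PASIPD leave the activity and participation objective without evidence, since the SIPSO measures participation separately, with a stated test-retest ICC of 0.91.

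The meaning of differ is undefined and could be settled in an analysis plan, so the 5% test is an assumption here. The adjective good may grammatically belong to reliability alone, and 0.30 is printed openly beside it. Neither point rescues the use of the score as a switch: that rule is in the article, and the 0.30 applies to it under either reading.

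**Conclusion.** The point holds in limited form. The stated validity of 0.30 is too low for the PASIPD to decide whether the primary fall models change, or for adjustment on it to be read as accounting for activity. Under the working assumptions, the switch catches a true 0.5 SD difference roughly one time in eight or nine with 46 per group, and the rule as a whole removes about a twentieth of the activity-related effect.

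These sizes depend on treating the accelerometer as truth. If it is only moderately accurate, moderate differences are still mostly missed and about 70–75% of the effect survives unconditional adjustment, but large differences would be caught about half the time. Part of the low power comes from the sample size and not the questionnaire. The randomised comparison without PASIPD remains sound. The fault lies in the data-driven switch and in any claim built on it.

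**What to change.** In the section on statistical analysis and sample size, delete the PASIPD group difference as a condition for changing the fall models, and keep the primary comparison free of PASIPD. If a PASIPD-adjusted model is wanted, specify it in advance as exploratory, using the mean of the six follow-up scores. State beside it that residual activity differences remain and that a non-significant PASIPD difference is not evidence of equal activity. In the section on activity and participation, give the 0.30 without calling it good. A measurement-error correction such as regression calibration is optional; it would rest on assumed validities and give wide intervals.

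The cost is a change of wording and, at most, one exploratory analysis of data already planned, with no new visits, devices or participants. The downside is that the trial will claim less about activity.

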#### Secondary outcomes (pre-post) – functional balance and mobility, and balance confidence

Pre-post measures will be obtained immediately before and after the initial period of training, and 6 and 12 months after the end of the initial training period. Functional balance and mobility will be assessed using the Berg balance scale (BBS [67]), the mini-Balance Evaluation Systems test (mini-BES [68]), and the ‘Timed Up & Go’ (TUG [69]). The BBS is a 14-item observational rating scale that provides a measure of functional balance. Participants will be asked to perform each of the 14 tasks, and their ability to perform each task will be rated on a scale from 0–4. The BBS shows good internal consistency (Cronbach’s α = 0.92–0.98) and good inter-rater (ICCs = 0.95–0.98), intra-rater (ICCs = 0.97), and test-retest (ICC = 0.98) reliability in the stroke population [70]. The mini-BES is a 14-item observational rating scale that assesses systems underlying balance control, including reactive balance control and dynamic stability during walking [68]. The mini-BES has good inter- (ICC = 0.96) and intra-rater reliability (ICC = 0.97) among individuals with stroke [71]. The BBS is commonly used in balance training studies and clinical settings; therefore, inclusion of this measure will allow for comparison between the proposed and previous trials. The mini-BES is a more specific measure and is less susceptible to floor and ceiling effects than the BBS [71]; thus, the mini-BES may be more likely to reveal training-related changes in reactive control and dynamic stability during walking. The TUG is a frequently-used test of functional mobility that is related to falls risk [72–74]. Participants will be seated in a 45 cm high chair with armrests, and will be instructed to rise from the chair, walk “as quickly as is safe” to a marker placed 3 m directly in front of the chair, to circle the marker, and then to return to the chair. Participants will be allowed to use the armrests to assist them with rising from the chair only if absolutely necessary. The time taken from the start command until the participant sits back in the chair will be measured. The TUG has excellent test-retest reliability among individuals with stroke (ICC = 0.95; [75]). The Activity-specific Balance Confidence (ABC) questionnaire [76] will be used to assess balance confidence during daily activities before and after training. The ABC asks participants to rate, on a scale from 0–100 %, how confident they would be performing 16 everyday tasks. The ABC shows good internal consistency (Cronbach’s α = 0.94) and test-retest reliability (ICC = 0.85) in individuals with stroke [77].

### Statistical analysis and sample size

Negative binomial regression will be used to compare fall rates between the two groups and logistic regression will be used to compare the proportion of fallers between the two groups. If the groups differ on prognostic factors (e.g., stroke severity) or on physical activity during the follow-up period (i.e., PASIPD scores) then multiple negative binomial/logistic regression will be used. Intent-to-treat analysis will be used; all individuals with some falls-monitoring data will be included in the analysis. Survival analysis may be considered if a large number of individuals do not complete the entire 12-month follow-up. Exploratory per-protocol analysis and/or comparison of fall rates between those who return for the ‘booster’ training sessions and those who do not may also be conducted. Repeated-measures analysis of variance, with group-by-time interaction, will be used to evaluate the effect of the interventions on secondary outcome measures (e.g., functional balance measures, balance confidence). The interaction effect will reveal if there is a greater pre- to post-training improvement in the perturbation training group compared to the control group.

The target sample size has been estimated using a formula for negative binomial regression described elsewhere [78]. Assuming a rate of falls in the control group of 1.75 per person per year [27], a reduction in rate of falling of 46 % in the perturbation training group [35], mean follow-up time of 11 months per person (i.e., some participants will be lost to follow-up before 12 months), level of significance (α) of 0.05, and power (1-β) of 0.8, we estimate that 37 participants per group will be required to show significant effects. From previous studies [32, 79], we expect that ~20 % of individuals will withdraw prior to completing the intervention. While many of these individuals will be willing to complete the 12-month falls monitoring period and could be included in intent-to-treat analysis, we conservatively assume that 20 % of individuals will withdraw from the study. Therefore, we will aim to recruit at least 46 participants per group (i.e., 92 participants total).

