### Outcome measures

Participants will be followed for 12 months following completion of the initial training period. During this time, falls, activity, and participation will be reported regularly. Balance confidence and functional balance and mobility will be assessed at study enrolment, immediately after the initial training period, six-months after the initial training period, and at the end of the 12 months follow-up. All data will be collected by a trained research assistant who is blinded to group allocation. Table 2 summarizes that measures that will be taken at each time point.

**Table 2 Tab2:** Summary of outcome measures and assessment time points

	Pre-training assessment	Post-training, interim and follow-up assessments	12-months follow-up period
Demographic and stroke information	✓		
Medical conditions	✓	✓	
Medications	✓	✓	
NIH-SS	✓		
CMSA	✓		
Lean-and-release test	✓		
BBS	✓	✓	
Mini-BES	✓	✓	
TUG	✓	✓	
ABC	✓	✓	
Falls reporting^a^	✓		✓
PASIPD^b^	✓		✓
SIPSO^b^	✓		✓

^a^Reported continuously throughout the 12-months follow-up period

^b^Questionnaires completed approximately every 2-months throughout the 12-months follow-up period

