#### Primary outcome – falls

A fall is defined as “an event that results in a person coming to rest unintentionally on the ground or other lower level” [14]. Participants will complete a 12-month falls monitoring period after the initial 6-week training period. Participants will be provided stamped addressed postcards containing a calendar to record falls, which they will complete daily. Participants will be asked to return each postcard to the research team fortnightly. Participants will receive a monthly study newsletter by mail containing health-related articles of interest, as well as a reminder to complete the postcards. If a participant does not return a postcard within two weeks, the research assistant will call them. In this telephone call, the research assistant will try to ascertain if the participant has experienced a fall in the previous two weeks. This method is considered the ‘gold standard’ for falls reporting [53]. Participants who report a fall on the calendar will be contacted by the research assistant to complete a short questionnaire in order to determine the cause and consequences of the fall.

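### Pre-training falls would enter the fall-rate model only if the groups happened to differ on them, so the precision they could give is not secured

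*Protocol article*

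**What the plan says.** Three places in the protocol article bear on this.

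- **Statistical analysis and sample size**, default model: "Negative binomial regression will be used to compare fall rates between the two groups". No covariate is named.
- **Same section**, next sentence, the rule for covariates: "If the groups differ on prognostic factors (e.g., stroke severity) or on physical activity during the follow-up period", multiple regression replaces the simple model. Stroke severity is given as an example, so the list of prognostic factors is open. Pre-training falls are not named.
- **Outcome measures, Table 2**: the row "Falls reporting^a" is ticked under the pre-training assessment as well as under the follow-up period. Its footnote covers the follow-up only: "Reported continuously throughout the 12-months follow-up period".

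The section on the primary outcome likewise describes only the period after training: "Participants will complete a 12-month falls monitoring period after the initial 6-week training period". The article does not say how, or over what period, the pre-training falls are asked.

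**The concern.** A covariate sharpens a fall-rate comparison because it predicts the outcome. Chance imbalance between the groups is not the source of that gain. A rule that waits for imbalance therefore leaves the covariate out in just those trials where the groups look alike, although the gain is available there too.

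A person's earlier falls are a natural predictor of later falls. The protocol accepts that participants differ in their tendency to fall: it stratifies on balance-recovery failures for that reason, and a negative binomial model presupposes spread between people. In the same paragraph the secondary outcomes use their pre-training values through repeated-measures analysis, while the primary outcome by default does not. At stake is the width of the interval for the fall-rate ratio in a trial planned on 37 analysed participants per group.

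**Working it through.** **Inputs from the protocol article (Statistical analysis and sample size).** "Assuming a rate of falls in the control group of 1.75 per person per year"; "a reduction in rate of falling of 46 % in the perturbation training group", so the second rate is 1.75 × 0.54 = 0.945; "mean follow-up time of 11 months per person", so t = 11/12 = 0.9167 years; α = 0.05; power 0.80; 37 per group. The dispersion k is not given, nor is the sidedness of the test; two-sided is taken here.

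**Step 1: reproduce 37.** The usual formula for the log rate ratio is

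n = (z₀.₉₇₅ + z₀.₈₀)² × [(1/t)(1/r₀ + 1/r₁) + 2k] / (ln RR)².

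- (1.960 + 0.842)² = 7.849
- (1/0.9167)(1/1.75 + 1/0.945) = 1.6296/0.9167 = 1.778
- (ln 0.54)² = 0.3797

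With k = 0, n = 7.849 × 1.778 / 0.3797 = 36.75, rounded up to 37. Under this two-sided form the stated figure is matched at k = 0, that is, at Poisson variance.

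**Step 2: the most a covariate could remove.** The variance of the log rate ratio at 37 per group is (1.778 + 2k)/37. Only the 2k part reflects differences between people, so its share, 2k/(1.778 + 2k), is a large-sample ceiling on what any baseline covariate can take out.

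| assumed k | n per group for 80 % power, unadjusted | power at 37 per group | ceiling on variance removed |
|---|---|---|---|
| 0 | 36.75 | 0.80 | 0 % |
| 0.5 | 57.4 | 0.61 | 1/2.778 = 36 % |
| 1 | 78.1 | 0.49 | 2/3.778 = 53 % |
| 2 | 119.4 | 0.34 | 4/5.778 = 69 % |

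**Step 3: what pre-training falls would remove.** This depends on k, on the recall window and on how closely a person's fall propensity before training tracks that afterwards. The article gives none of the three. Counts were simulated with gamma frailties, 37 per group, 300 runs per setting, and fitted by negative binomial regression with and without log(baseline falls + 0.5). A Poisson fit was used where the negative binomial fit failed. Assumed: k from 0.5 to 2, window 6 to 12 months.

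| frailty correlation | fall in variance of the log rate ratio |
|---|---|
| 0.3 | about 1–3 % |
| 0.6 | about 4–15 % |
| 1.0 (fully stable) | about 11–49 % |

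Two settings with a 12-month window, where simulation error on power is about 3 points:

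- k = 1, correlation 0.6: standard error 0.316 to 0.300; (0.300/0.316)² = 0.90, a fall of about 10 %; power about 0.52 to 0.56.
- k = 2, correlation 1.0: standard error 0.386 to 0.275; (0.275/0.386)² = 0.51, a fall of about 49 %; power about 0.39 to 0.61.

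**Step 4: imperfect recall and the null.** A separate simulation (700 to 1000 trials per setting) with correlation 0.6 and 30 % of earlier falls forgotten gave a variance reduction of about 4–7 % and 3 to 5 points of power. Null rejection was 4–7 % unadjusted and 4–8 % adjusted, with the 8 % at k = 2. Part of any power gain at high dispersion may therefore be apparent.

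**The case against.** The best case for the plan has four parts.

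1. *Covariates are a matter for the analysis plan, and the list of prognostic factors is open.* Fall history could indeed enter under the stated rule, and that stands. But the article does not leave the matter to a later document: it fixes when covariates enter, and the trigger is observed difference. An open list does not cure that.
2. *The pre-training item is not shown to be a baseline value of the primary outcome.* This stands. The outcome is a daily calendar kept after training. The earlier item has no stated window or format and might even be a yes/no question. The wording of a form is commonly left out of an article, so its absence is no fault in itself. It does limit what can be claimed for the covariate.
3. *The gain may be small.* This stands too. It is nil at the dispersion that reproduces 37 in the two-sided formula, and a few per cent at modest correlation.
4. *The comparison was with no adjustment at all.* The gain over and above the stratification factor, balance-recovery failures, was not examined. It may be smaller than the figures shown if that factor is also in the model.

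**Conclusion.** The point holds as one about efficiency. As written, the rate comparison is unadjusted unless the groups are seen to differ, so the precision carried by pre-training falls is obtained only by chance. The likely size is modest: about 1–15 % of the variance at frailty correlations of 0.3 to 0.6, given assumed k of 0.5 to 2 and a 6- to 12-month window. The 11–49 % range is an upper bound that needs a fully stable propensity.

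A reader might infer more, and the article does not support it:

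- *That the plan discards pre-training falls.* The conditional rule could admit them.
- *That the trial loses a large, known amount of power.* No loss can be derived from the article. The low unadjusted powers in the first table come from assumed overdispersion and concern the sample size, not the missing covariate.
- *That the unadjusted comparison is biased.* It is not: this is a randomised comparison. Nor would adjustment introduce bias, since the initial assessment precedes randomisation (Group allocation and blinding) and recall error cannot depend on the group.
- *That the same gain applies to the proportion of fallers.* In a logistic model, adjustment changes the odds ratio to one conditional on baseline falls, and a narrower standard error should not be expected.

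**What to change.** State in the analysis section that pre-training falls, counted over one stated recall window, are a covariate in the primary negative binomial model whatever the observed balance. For this covariate, that replaces the imbalance trigger. If the item is collected as a count, log(count + 0.5) is a workable form. Set the same recall window on the pre-training form for every participant.

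If the covariate is also used in the logistic model for fallers, say that the odds ratio is then conditional on baseline falls, and claim no gain in precision there.

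The cost is one sentence and one form item. There are two small downsides. Recalled falls are imprecise, which shrinks the gain. And null rejection of the adjusted test should be checked by simulation under high dispersion before the model is fixed, given the figure of about 8 % at k = 2.

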Despite control challenges associated with executing reactive steps, individuals with impaired balance control are increasingly dependent on these stepping responses because they are the last option to prevent falling. Because stroke survivors are at a high risk of falls, it is essential to develop approaches to re-train compensatory stepping after stroke. There is compelling evidence that physical exercise prevents falls among older adults [28]; however, no exercise intervention has effectively reduced risk of falls among individuals with stroke [29, 30]. More specific exercise, that is, perturbation training involving repeated exposure to applied balance disturbances, is necessary to achieve improvements in the control of fast reactive movements [22, 31–34]. Perturbation training is an emerging and promising treatment strategy for preventing falls [35]. The novelty of perturbation training is in the focus on speed of processing and execution of limb movements, as well as rapid restabilization; this differs from ‘traditional’ balance training programs using voluntary movements that allow participants to control speed. Such training is specific to the demands of balance recovery reactions to prevent a fall following a ‘real life’ loss of balance.

The primary objective of this study is to determine if a novel perturbation-based training program focused on improving reactive stepping in individuals with chronic stroke will reduce the risk for falls in the community. Secondary objectives are to determine the effect of perturbation training on balance confidence and activity restriction, and functional balance and mobility. Our primary hypothesis is that individuals with chronic stroke who complete perturbation training will be less likely to experience a fall up to 12-months following completion of the program, compared to individuals who complete a ‘traditional’ balance training program (control group). Our secondary hypothesis is that, compared to individuals in the control group, individuals with stroke who complete the perturbation training program will show: increased balance confidence; increased participation in daily activities in the year following completion of the program; and greater gains in functional balance and mobility.

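### Logistic regression on faller yes/no ignores length of follow-up, so people who leave monitoring fall-free in effect count as non-fallers, and unequal loss biases the comparison

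*Protocol article*

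**What the plan says.** Under *Statistical analysis and sample size*, the protocol article plans two analyses of falls: negative binomial regression for rates, named first, and a yes/no analysis in which "logistic regression will be used to compare the proportion of fallers between the two groups". The analysis set is broad: "all individuals with some falls-monitoring data will be included in the analysis". No offset, minimum follow-up or imputation is stated for the yes/no model.

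The same section expects incomplete follow-up. Its sample size uses a "mean follow-up time of 11 months per person (i.e., some participants will be lost to follow-up before 12 months". Its one provision for this is that "Survival analysis may be considered if a large number of individuals do not complete the entire 12-month follow-up".

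Under *Primary outcome – falls*, monitoring begins only when training has ended: "Participants will complete a 12-month falls monitoring period after the initial 6-week training period". In the *Background*, the primary hypothesis is that the perturbation group "will be less likely to experience a fall up to 12-months following completion of the program".

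**The concern.** A yes/no model that keeps everyone with any diary data must give a value to a person who leaves after one month without a fall. With no term for time at risk, the natural value is non-faller, the same as for a person observed fall-free for 12 months. Two things follow. The 12-month faller proportion is too low in both groups. If one group loses more people during monitoring, or loses them earlier, that group appears to have fewer fallers whatever the training did. More loss under perturbation training would flatter it, and more loss among controls would hide a benefit.

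The primary hypothesis is worded as a 12-month risk, which is the quantity this analysis is meant to estimate.

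**Working it through.** **Inputs from the protocol.** "Assuming a rate of falls in the control group of 1.75 per person per year"; "a reduction in rate of falling of 46 % in the perturbation training group"; mean follow-up 11 months; two-sided α 0.05 (sidedness assumed), power 0.80; 46 recruited per group.

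**The plan's own figure.** The usual negative binomial formula is n = (z₀.₉₇₅ + z₀.₈₀)² × [(1/t)(1/r₀ + 1/r₁) + 2k] / ln(RR)². With r₀ = 1.75, r₁ = 1.75 × 0.54 = 0.945, t = 11/12 and k = 0, it gives 7.849 × 1.778 / 0.380 = 36.75, so 37 per group, as stated. Then 37/0.8 = 46.25; the protocol states 46.

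**Assumptions.** Both groups fall at 1.75 a year (no true effect). Dispersion k is 0.5 or 1, because the protocol states none. A share d of a group leaves monitoring, unrelated to falls, and a leaver with no recorded fall is coded non-faller.

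**Formulas.**
- Probability of a fall by time T (years): P(T) = 1 − (1 + 1.75kT)^(−1/k). At 12 months this is 0.716 (k = 0.5) or 0.636 (k = 1).
- Average of P(T) for people leaving evenly over the year: 0.467 (k = 0.5) or 0.422 (k = 1).
- Observed proportion = (1 − d) × P(1) + d × (P at leaving, or its average).

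**One case in full** (k = 0.5, loss 20% versus 5% over the year):
- 0.8 × 0.716 + 0.2 × 0.467 = 0.666
- 0.95 × 0.716 + 0.05 × 0.467 = 0.703
- Odds ratio = (0.666/0.334)/(0.703/0.297) = 0.84

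**Results** (perturbation versus control; observed proportions, then odds ratio; the true odds ratio is 1.00):

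| Loss during monitoring | Mean follow-up, months | k = 0.5 | k = 1 |
|---|---|---|---|
| 16.7% vs 16.7%, over the year | 11.0 | 0.674 vs 0.674, 1.00 | 0.601 vs 0.601, 1.00 |
| 20% vs 10%, over the year | 11.1 | 0.666 vs 0.691, 0.89 | 0.593 vs 0.615, 0.91 |
| 20% vs 5%, over the year | 11.25 | 0.666 vs 0.703, 0.84 | 0.593 vs 0.626, 0.87 |
| 20% vs 10%, all at 3 months | 10.65 | 0.638 vs 0.677, 0.84 | 0.570 vs 0.603, 0.87 |
| 20% vs 10%, all at 1 month | 10.35 | 0.599 vs 0.657, 0.78 | 0.535 vs 0.585, 0.81 |
| 20% vs 5%, all at 3 months | 10.875 | 0.638 vs 0.696, 0.77 | 0.570 vs 0.620, 0.81 |
| 20% vs 5%, all at 1 month | 10.625 | 0.599 vs 0.686, 0.68 | 0.535 vs 0.611, 0.73 |
| 33% vs 0%, over the year | 11.0 | 0.633 vs 0.716, 0.68 | 0.565 vs 0.636, 0.74 |

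The first row shows the understatement without any imbalance: 0.674 against a true 0.716, and 0.601 against 0.636.

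**Sensitivity to k.** For 20% versus 10% over the year, the odds ratio is 0.84 at k = 0 (the value that reproduces 37) and 0.93 at k = 2.

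**Scale.** With full follow-up, the planned 46% rate reduction corresponds to a faller odds ratio of 0.46 (k = 0.5) or 0.54 (k = 1).

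**False-positive rate, 46 per group, nominal 5%.** Loss over the year of 20% versus 10% gives 5.7% (k = 0.5) or 5.1% (k = 1). Loss of 20% versus 5% gives about 6 to 7% by normal approximation. In simulations of 1,000 trials with heavier imbalance (30% versus 10% over the year or within 3 months, and 33% versus 0%; k of 0 and 1), logistic regression rejected in 5.9 to 25.1%. A log-rank test on time to first fall, including a case with equal loss, rejected in 4.7 to 5.8%.

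**The case against.** Several points on the other side stand.

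- **The 20% is a different quantity.** A reader might take it as the expected loss during monitoring. The protocol ties it to withdrawal before the intervention is completed. People who leave then and give no diary data are outside the analysis set, so they are not scored as non-fallers. Others may stop training yet be monitored for the full 12 months. The only figure for loss during monitoring is the 11-month mean, so the 20% shares in the table are assumptions.
- **Early, one-sided loss is not predicted.** Putting all loss at 1 to 3 months takes mean follow-up to between 10.35 and 10.9 months, below the protocol's 11. Contact time and booster sessions are matched between groups, both complete the same diary, and reminders, telephone calls and an alternative contact support retention. The training tasks do differ, so unequal loss is possible, but nothing in the protocol establishes it.
- **The bias is modest against sampling error.** At k = 1 and 20% versus 5% over the year, ln(0.87) is about −0.14, against a standard error of the log odds ratio of about 0.43.
- **The trial does not rest on this model alone.** The hypothesis wording might suggest that it does. The rate model is named first, drives the sample size and can account for time at risk.
- **The coding of early leavers is implied, not written,** and an analysis plan could settle it.

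The last point does not dispose of the matter. The article itself fixes the model and the analysis set, and together they leave no stated place for time at risk. The survival option does not repair this: it is discretionary, has no threshold, and looks at how many people fail to complete rather than at imbalance. A reader might also infer that the choice would be made with outcomes in view. The text does not say so, since completion could be judged blind to group and falls.

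**Conclusion.** The point holds at moderate strength. As written, the faller comparison understates the 12-month proportion in both groups, and its odds ratio is biased whenever loss during monitoring is unequal. For the loss shares of 20% versus 5% or 10%, spread over the year, the null odds ratio is about 0.84 to 0.91. It ranges from 0.68 to 0.87 if those losses all come at 1 to 3 months. With equal loss and no true effect it is 1.00. An extreme imbalance of 33% versus 0% is compatible with the 11-month mean and gives 0.68 to 0.74 even when spread over the year.

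These sizes rest on the protocol's 1.75 falls a year, an assumed k of 0.5 to 1, assumed loss shares, loss unrelated to falls, and fall-free leavers coded as non-fallers. The protocol does not support the stronger reading that a false effect in favour of perturbation training is to be expected: it gives no loss by group, and the bias could run either way. The reason to change the plan is that a better-suited method is available at almost no cost.

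**What to change.** Make time to first fall, censored at the last diary day, the planned analysis of the faller outcome. Report the Kaplan–Meier 12-month faller proportion by group and a Cox model stratified by the randomisation strata (site and frequency of balance-recovery failures). This replaces the conditional sentence on survival analysis. Keep the negative binomial model for fall rates, with follow-up time as an offset. Logistic regression can stay as a sensitivity analysis, for example in participants with complete 12-month diaries.

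A binary model with complementary log-log link and log follow-up time as offset is possible but not equivalent to Cox, because it assumes a constant hazard.

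The cost is wording only. Falls are already recorded on daily calendars, although a fall learnt of by telephone may be dated only to the fortnight. The downside is small: censoring assumes that loss is unrelated to fall risk. Follow-up by group and a sensitivity analysis for informative loss should therefore be reported.
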